# Study and treatment protocol

## Field procedures

The headmasters of the schools will be informed about the purpose and procedures of the study. Once informed consent is obtained, the objectives and procedures will be explained to the teachers, schoolchildren and their parents and written informed consent (see Appendix 1) by the participants’ parents/legal guardians will be obtained.

Field procedures are as follows. The study will be conducted between March and May 2009 (for exact protocol see Appendix 2). In an in-depth baseline survey before treatment, approximately 2000 children will be asked to submit 1 stool sample of sufficient size (at least 5 g) to perform the anticipated examinations. On the first day of the survey, about 200 participants will be given a plastic container and invited to bring a fresh stool specimen the following morning. Upon collection, a unique identification number will be attached to the container and demographic data will be collected (e.g., age and sex).

This procedure will be repeated over several days, entering ~200 additional schoolchildren every day up to a total of 2000 children. One of the inclusion criteria for the randomized drug trial is an infection with *T. trichiura* (see point 5.). We anticipate that with an expected prevalence of 25% of *T. trichiura* infections and with a compliance of 95% working for 2-3 weeks in Kinyasini and Chaani schools will suffice to obtain the required sample size of at least 540 children infected with *T. trichiura*. In addition those children diagnosed with *A. lumbricoides* and/or hookworm will also be attributed to one of the 4 treatment regimens, but their numbers are not included into the sample size calculations. Before the onset of the trial, each individual included into the trial will be physically examined by a medical assistant for exclusion criteria.

Once all samples have been collected and analysed, a randomized treatment list allocating the IDs of the ~540 children infected with *T. trichiura* and of the remaining children infected with *A. lumbricoides* and/or hookworm to one of the 4 treatment regimens will be prepared. On the day before treatment the selected children will be given another stool container and they will be asked to provide another stool sample the following morning. On the day of treatment the stool samples will be collected and all children’s weights will be recorded. The children will be allocated to one of four groups, as follows:

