## Laboratory procedures

All stool samples will be transferred to the HCLU on the day of collection, and will be examined by experienced laboratory technicians and the PhD-student. At the baseline screening, 2 Kato-Katz thick smears *(*41) from one stool sample per individual using 41.7 mg of stool will be prepared and examined quantitatively for the presence of hookworm eggs after a clearing time of 20-30 min, and subsequently for *A. lumbricoides* and *T. trichiura* eggs. The eggs of *A.* *lumbricoides*, hookworms and *T. trichiura* will be counted and recorded separately. From 250 randomly selected stool samples 1-2 g will be preserved in SAF for subsequent examination with the FLOTAC method *(*54).

From children included into the randomized controlled trial and thus providing another stool sample at the day of treatment and 2 consecutive stool samples for the follow up, a double Kato-Katz thick smear will be prepared and examined. At the days of follow up 1-2 g of stool, from those individuals examined with FLOTAC before treatment and who have been included in the trial, will again be preserved in SAF for subsequent examination with the FLOTAC method. All laboratory investigations will be blinded, e.g. the technicians examining the Kato-Katz slides or FLOTAC apparatus will not be aware of the treatment regimen of the participants. A random sample of 10% of the Kato-Katz thick smears will be re-examined by a Tanzanian senior laboratory technician for quality control.

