# Sample size

Sample size calculations are based on the differences in CR of albendazole or mebendazole versus albendazole and ivermectin against *T. trichiura*.

The CRs of treatment with albendazole (400 mg single oral dose) and mebendazole (500 mg single oral dose) have been reported in a recent meta-analysis to be 28% (95% CI, 13%-39%) and 36% (95% CI, 16%-51%) for *T. trichiura*; 88% (95% CI, 79%-93%) and 95% (95% CI, 91%-97%) for *A. lumbricoides*; and 72% (95% CI, 59%-81%) and 15% (95% CI, 1%-27%) for hookworm infections *(*34).

The CR of the combination treatment of albendazole (400 mg single oral dose) plus ivermectin (200-400 µg/kg) as single therapy were reported from Haiti and the Philippines for the major soil-transmitted helminths and indicated to be 79.6% and 65.1%, respectively for *T. trichiura*, 100% and 78.1%, respectively for *A. lumbricoides* and 100% for hookworm infections *(38,* 55).

No relevant references on a combination therapy of mebendazole and ivermectin exist according to a recent review on the efficacy and safety of drug combinations *(*35).

Information about CR and ERR of albendazole, mebendazole and ivermectin are also available for Zanzibar. The CRs of a single dose of albendazole (400 mg) and mebendazole (500 mg) were assessed in a single-blind randomized controlled trial performed in Pemba, Zanzibar, in 1992/93 and were 10.5% and 14.2% for *T. trichiura*, 98.9% and 97.8% for *A. lumbricoides* infections and 56.8% and 22.4% for hookworm *(*51). ERRs for albendazole and mebendazole in the same study were 73.3% and 81.6% for *T. trichiura*, 99.6% and 99.3% for *A. lumbricoides* infections and 97.7% and 82.4% for hookworm *(*51).

The CR and ERR of a single dose ivermectin (200 µg/kg) were assessed in Unguja in 1994 and were 11.3% and 58.9% for *T. trichiura*, 100% and 100% for *A. lumbricoides* infections and 0% and 0% for hookworm *(*18).

The sample sizes indicated in **Table 1** were calculated in Microsoft Excel with an equation given by Fleiss *(*56):

7.85*((A1*(1-A1))+(B1*(1-B1)))/(ABS(A1-B1))^2+2/ABS(A1-B1)+2

Where A1 is the estimated CR from treatment A (e.g. albendazole or mebendazole) and B1 is the estimated CR from treatment B (e.g. albendazole plus ivermectin or mebendazole plus ivermectin).

Using a significance level of 5% to detect greater efficacy of one treatment, and a power of 80%, the following table indicates the required number of individuals **per treatment group** at different CRs:

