**Table 1: Cure rates for *T. trichiura***

**Treatment A (albendazole or mebendazole)**

| **Treatment B**  **(albendazole or mebendazole plus ivermectin)** | 15% | 20% | 30% | 35% | 40% | 45% | 50% | 55% |
| --- | --- | --- | --- | --- | --- | --- | --- | --- |
| 60% | 21 | 27 | 48 | 69 | 106 | 185 | 407 | 1573 |
| 65% | 17 | 21 | 36 | 48 | 69 | 105 | 182 | 395 |
| 70% | 14 | 18 | 28 | 36 | 48 | 67 | 102 | 175 |
| 75% | 12 | 15 | 22 | 27 | 35 | 47 | 65 | 97 |
| 80% | 10 | 12 | 18 | 21 | 27 | 34 | 44 | 61 |
| 85% | 9 | 10 | 14 | 17 | 21 | 25 | 32 | 41 |
| 90% | 8 | 9 | 12 | 14 | 16 | 20 | 24 | 29 |

Based on the given information we estimate the CR of albendazole/mebendazole for *T. trichiura* infections to be between 20% and 45% and the CR of the combination of albendazole/mebendazole plus ivermectin to be between 65% and 80%. Hence, a sample size of at least 105 participants per treatment group is needed for significance analysis.

In the proposed study sites, the prevalence of *T. trichiura* infections is most likely to be above 30% and the compliance is estimated to be around 90%. These assumptions are based on a study performed in Kinyasini and Chaani schools in 2007 where 25.9% of the children were found to be infected with *T. trichiura* after examination of 1 stool sample and 47.9% after examination of 3 stool samples with the Kato-Katz method and where the compliance to submit 1-3 stool samples was >85%. In view of the required number of cases per group, and allocating for patients lost to follow-up, at least 2000 subjects would have to be screened so that 500-600 infected individuals infected with *T. trichiura* can enter the trial (see Appendix 5).

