**Week 5 and 6**

- Prepare a list containing the IDs of the 500-600 children infected with *T. trichiura*

- Prepare a list containing the IDs of the remaining children infected with *A. lumbricoides* and/or hookworm

- Assign the 500-600 children infected with *T. trichiura* randomly to one of the four treatment regimens

- Assign the remaining children infected with *A. lumbricoides* and/or hookworm randomly to one of the four treatment regimens

- Check children infected with *T. trichiura*, *A. lumbricoides* and/or hookworm for exclusion criteria

- Distribute labelled stool container to all children included into the randomized trial

- Collect filled stool containers from all children and transport them to the laboratory

- Prepare 2 Kato-Katz slides from each stool sample and examine as described beyond

- Distribute the drugs to the children according to the randomized list

- Ask child to swallow the drug with clean water and check that the tablet has been swallowed by looking into the mouth and under the tongue

- Monitor and record side effects for 3 hours provide medical assistance where necessary

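### The treatment list is drawn after all screening counts are known, but neither the list nor the cure-rate comparison uses egg count: no bias, but inexpensive precision is given up

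*Combined protocol and SAP*

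**What the plan says.** Field procedures fixes the timing: "Once all samples have been collected and analysed, a randomized treatment list allocating the IDs of the ~540 children infected with" *T. trichiura*, together with the remaining infected children, is prepared before treatment. The information available by then is substantial. Laboratory procedures states "At the baseline screening, 2 Kato-Katz thick smears" per child, read quantitatively with each species counted separately. Under Appendix 3 the ID number itself identifies the school.

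Appendix 3 (Week 5 and 6) describes the allocation. One list holds the 500-600 children with *T. trichiura*. For the others the instruction is "Prepare a list containing the IDs of the remaining children infected with" *A. lumbricoides* and/or hookworm. Each list is then assigned "randomly to one of the four treatment regimens". No blocking or stratification by egg count, school or co-infection is described. Appendix 8 shows 135 children per arm, 114 treated and 103 evaluable.

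Data analysis says that cure rates and egg reduction rates will be compared, but names no test and no baseline covariate. Initial parasite load is mentioned only for the adverse-event analysis.

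**The concern.** Cure means finding no eggs at follow-up, and a child who starts with few eggs is more likely to be read as negative. Background (Control of soil-transmitted helminth infections) itself says that Kato-Katz often misses light infections. Baseline count is therefore a plausible predictor of the primary outcome. If it is, chance differences in worm load between arms add avoidable variance to the cure-rate difference.

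Balancing is usually hard because children arrive one at a time and small blocks can make the next allocation guessable. Neither applies here: the list is drawn once, for everyone, with the counts in hand. The opportunity to balance ends when the list is drawn. The opportunity to adjust does not, but it should be specified in advance.

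The point concerns cure rate only. The egg reduction rate under Study type and measurement is built from each child's own counts before and after treatment.

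**Working it through.** **1. The plan's own figure.** The stated equation is "7.85*((A1*(1-A1))+(B1*(1-B1)))/(ABS(A1-B1))^2+2/ABS(A1-B1)+2". At the hardest planned contrast, 45% v 65%:

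7.85 × (0.2475 + 0.2275)/0.04 + 2/0.20 + 2 = 93.2 + 10 + 2 = 105.2.

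This agrees with "Hence, a sample size of at least 105 participants per treatment group is needed for significance analysis". The constant 7.85 is (1.960 + 0.842)², that is, two-sided 5% and 80% power.

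**2. Evaluable children.** Appendix 8 gives 135 − 7 − 14 − 11 = 103 per arm. The variance of the crude difference at 45% v 65% is (0.2475 + 0.2275)/103 = 0.00461, an SD of 6.8 points. Power with 103 per arm (two-sided 5%, normal approximation, no continuity correction) is 82.7%.

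**3. Why egg count should matter.** Follow-up uses four smears of 41.7 mg, or 0.1668 g. As an illustration, apply the 73.3% albendazole egg reduction quoted under Sample size equally to every child:

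- starting at 48 EPG: 48 × 0.267 × 0.1668 = 2.1 expected eggs on four smears;
- starting at 480 EPG: 21.4 expected eggs.

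This gives the direction. It does not give the strength, which the documents do not report.

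**4. Share of variance that balancing can remove, complete blocks.** Assume that cure in arm A has probability mA(x), logistic in standardised log egg count x, and likewise mB(x), with the overall cure rates held at the planned values. Then

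share = [Var(mA) + Var(mB) − Var(mA − mB)/4] / [pA(1 − pA) + pB(1 − pB)].

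| Odds ratio per SD (assumed) | 45% v 65% | 20% v 80% |
|---|---|---|
| 1.25 | 1% | 1% |
| 1.5 | 4% | 3% |
| 2 | 9% | 7% |
| 2.5 | 15% | 11% |
| 3 | 19% | 15% |
| 4 | 26% | 20% |
| 5 | 31% | 25% |

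In terms of tertiles of egg count at 45% v 65%, outer tertiles lying 10, 20 or 30 points either side of the middle give 3%, 11% and 25%.

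**5. After the planned losses.** If children are lost at random after blocking, the removable part shrinks by roughly 103/135 = 0.763. At 45% v 65%, with complete-block shares of 3.6%, 9.4%, 14.7% and 21% for odds ratios of 1.5, 2, 2.5 and 3.3, this leaves 2.7%, 7.2%, 11.2% and 16.0%. One simulation with this loss gave 7%, 11% and 16% for odds ratios of 2, 2.5 and 3.3. Another gave 1%, 3%, 9% and 14% for all four. A fair summary is 1-16%.

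**6. What it buys.** A variance reduction R makes 103 children act like 103/(1 − R):

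- R = 5%: 108, power 84.6%;
- R = 10%: 114, power 86.5%;
- R = 15%: 121, power 88.4%.

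**7. Bias and adjustment.** In 20,000 simulated trials per setting at 45% v 65%, the unstratified design gave a mean difference of 0.200 for a true 0.20. Post-stratifying the analysis on egg-count quintiles, without touching the list, recovered 11 of 15 percentage points at an odds ratio of 2.5, 18 of 21 at 3.3, and about none at 1.5.

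**The case against.** The strongest reply is that simple randomisation is valid and its ordinary standard error already allows for chance imbalance. That stands. A reader might infer from the missing stratification that the reported cure rates will be distorted; the documents do not support this, and step 7 shows no bias.

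A reader might also want one firm figure, such as a loss of 15-23% of the variance. At 45% v 65% this requires an odds ratio of about 2.5-3.5 per SD, and at 20% v 80% about 3.0-4.6, with every block intact. Nothing in the documents establishes either value. Some 24% of each arm is expected to drop out, so if losses are random only about 0.763⁴ = 34% of blocks would stay whole.

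A third tempting reading is that uneven co-infection harms the *A. lumbricoides* and hookworm results. With 1800 × 16.5% = 297 and 1800 × 22.5% = 405 infections, unrestricted allocation gives average gaps of about 18 and 21 between the largest and smallest arm. With equal arms, as Appendix 8 implies for *T. trichiura*, and independent infections, the gap is about 14 for each. Even the unrestricted version raises the variance of a two-arm difference by only about 1%, and Field procedures leaves the children without *T. trichiura* out of the sample size.

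Power is also ample for much of the planned range: with 103 per arm it is 98.9% at 36% v 65% and above 99.9% at 28% v 65%. This limits the point but does not remove it. The Significance section wants to learn which regimen is most efficacious, and the plan's equation shows how small the trial is for the closer contrasts. For 65% v 80% it gives 7.85 × 0.3875/0.0225 + 13.3 + 2 = 150.5, so about 151 per arm. For 28% v 36% it gives 7.85 × 0.432/0.0064 + 25 + 2 = 556.9, so about 557.

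Finally, adjustment at analysis recovers much of the gain when the link is strong, so the list is not the only remedy. That is correct, but no such adjustment is planned.

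**Conclusion.** The point holds as a matter of efficiency. The counts are known before the list is drawn, the list uses only the split into two species groups, and no baseline egg count is named for the cure-rate comparison. The consequence is extra variance, not bias.

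The size is an assumption: about 1-31% of the variance for odds ratios of 1.25-5 per SD with complete blocks, and about 1-16% for odds ratios of 1.5-3.3 after the loss to 103 per arm. These ranges rest on a logistic link, on cure rates at the planned values and, for the second, on losses unrelated to egg count. If the link is weak, almost nothing is gained. Blocking alone does not finish the job either: an unadjusted test after blocking does not credit the gain in its standard error. The change is worth making because it is nearly free, not because a conclusion has been shown to be at risk.

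**What to change.** **Field procedures and Appendix 3 (Week 5 and 6), before the list is drawn.** Sort the *T. trichiura* list by school and then by screening *T. trichiura* count; co-infection status may be added. Sort the second list by school and infecting species. Cut each list into consecutive blocks of four and allocate one child per regimen at random within each block, using a program with a recorded seed.

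**Data analysis.** Keep the crude cure rates as the descriptive result. Pre-specify the comparison of cure rates as stratified by, or adjusted for, school and log baseline *T. trichiura* count, and report it as a difference in cure rates with its confidence interval. State whether the baseline is the screening count alone or also includes the treatment-day sample. For the other two species, use the count of that species. This adjustment is worthwhile even if the list is not blocked.

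**Cost.** About an hour of programming and no field work. Losses after allocation will break some blocks, which reduces the gain but does no harm.

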## Safety of the benzimidazoles

On Zanzibar, multiple studies on the efficacy of mebendazole, albendazole, ivermectin and albendazole plus ivermectin have been conducted *(18-20, 45, 46, 48, 50,* 51). Actively assessed, no severe side effects were recorded for albendazole or ivermectin in a trial conducted in Unguja in 1994, and mild side effectswere of transient nature for both treatments *(*18). Although not actively assessed, no adverse events were reported after mebendazole treatment in the week following the administration of anthelminthics in Pemba *(*48). No severe adverse reactions were reported from a trial conducted in Zanzibar in 2006 to assess the safety of triple drug co-administration (albendazole plus ivermectin plus praziquantel) *(*19). The combined treatment of albendazole and ivermectin is successfully and safely applied to treat the Zanzibari population since 2001 in the frame of the GPELF *(*20). In general, the side effects of albendazole and mebendazole, at the dosage recommended for deworming, have been described as negligible and self-limiting *(*52). However, even if the single applications of albendazole, mebendazole and ivermectin are reported to be safe, to our knowledge, there are no reports on the combined treatment of mebendazole and ivermectin. Hence, the safety of the latter drug combination needs to be confirmed.

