1. Single-dose albendazole group; children will receive one tablet of albendazole (400 mg) and a placebo resembling ivermectin (number of tablet according to weight).
2. Mebendazole group; children will receive a single dose of mebendazole (500 mg) and a placebo resembling ivermectin (number of tablet according to weight).
3. Albendazole plus ivermectin group; children will receive one tablet of albendazole (400 mg) plus ivermectin tablets according to their weight (200 µg/kg).
4. Mebendazole plus ivermectin group; children will receive one tablet of mebendazole (500 mg) plus ivermectin tablets according to their weight (200 µg/kg).

The participants will be asked to swallow the drugs with clean water and the health worker administering the drugs will check that the tablets have been swallowed by looking into the mouth and under the tongue. During the entire treatment phase and for one additional hour, a clinician will be present for supervising drug intake, monitoring and registering acute adverse events of the four drug regimens and to provide medical assistance where necessary. The medical assistant will be provided with a complete list of possible adverse events of the respective drug. In case of adverse events, appropriate medical action will be taken, e.g. administration of drugs for relief.

The children will be kept under medical supervision for one hour after treatment. The staff of the Public Health Centres (PHC) located nearest to the two schools (Upenja and Chaani) will be informed and undergo a pharmacovigilance training in the week before treatment. Additionally, the PHCs will be provided with first aid drugs and will remain open for 24 hours on the day of treatment. Children, parents and teacher will be informed that in case of any adverse reaction they can refer cases to the PHC at day and night time for 24 hours. Forty eight hours after treatment, solicited adverse events due to the treatment will be assessed by a previously tested questionnaire (see Appendix 3). The onset and duration of the side effects will be recorded and graded as follows:

- *mild:* present but not requiring any interference;
- *moderate:* (1) present and requiring medication for symptomatic relief as requested by the affected people or (2) present and interfering with normal daily activities; and
- *severe:* present and required medical intervention beyond symptomatic relief.

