# Assessment of benefits and risks for the study population

Benefits of participating in the study will be as follows. First, participants will receive free laboratory investigations for soil-transmitted helminthiasis and will be informed in person about their parasitological and clinical results. Second, the infected participants will receive free treatment. Anthelminthic treatment can improve the children’s general health status, including better uptake of nutrition, reduced anemia, and improved growth and cognitive development. Third, at population level, the assessment of a more effective treatment regimen against *T. trichiura* and the early detection of a potential resistance against certain anthelminthic drugs in the frame of this study can lead to appropriate policy recommendations by the Zanzibari government and the WHO and enhance the success of helminth control in Zanzibar and elsewhere.

Risks to participate in the study are due to the side effects that may be associated with anthelminthic drugs and that are generally reported to be mild, transient and self-limiting. Side effects can include fatigue, headache, dizziness, allergic reactions, shivering, abdominal pain, nausea, vomiting, diarrhea or fever.

Medical personal and the drivers of the helminth control team will remain with the treated study participants for one hour after treatment and in case of any acute adverse reaction refer the child to the nearest PHC. The PHCs will remain open for 24 hours on the day of treatment and will be provided with first aid drugs before treatment starts. Children, parents and teachers will be instructed that in case of any adverse reaction they can refer cases to the nearest PHC at day and night time for 24 hours after treatment. In case of any adverse reaction the participant will be treated free of charge.

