# Data analysis

The following data will be available for each individual:

Name

Age

Sex

Date of treatment

Drug used

Date of follow up

Parasitological data of first stool examination (double Kato-Katz thick smear)

Parasitological data of second stool examination (double Kato-Katz thick smear and single FLOTAC)

Parasitological data of follow up (2 stool samples with 2 Kato-Katz thick smears per sample and single FLOTAC)

Data on adverse events of treatment after 3 h (acute) and 72 h (solicited).

All data will be entered twice in Microsoft Excel version 10.0 (2002 ® Microsoft Corporation) by local staff in Zanzibar. Datasets will be compared using EpiData version 3.1 (EpiData Association; Odense, Denmark), and discrepancies removed based on the original records by the PhD student ([name]) when back in Switzerland. Statistical analyses will be carried out by the PhD student with JMP version 5.0.1 (SAS Institute; Cary, NC, United States of America). The CR of the treatments and the ERR will be compared for each drug according to the results of either the Kato-Katz or the FLOTAC method or the combination of both methods.

In addition, the frequency and severity of acute and solicited adverse events of the different drug regimens will be compared. The latter analysis will try to seek differential effects according to age, sex and initial parasite load.

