# Conflict of interest

None of the investigators has any conflict of interest concerning the work or drug application reported in this protocol. The drugs (albendazole, mebendazole and ivermectin) as well as the placebo (aspartam) were bought from pharmacies in Switzerland and France. No drugs were donated and no drug company is involved in the formulation of this study protocol.

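### Acute adverse events are sought with a list worded by drug, and blinding is stated only for the laboratory, so unequal ascertainment between regimens is not excluded

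*Combined protocol and SAP*

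**What the plan says.** All references are to the combined protocol and SAP.

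- **Who registers acute events.** Field procedures: "a clinician will be present for supervising drug intake, monitoring and registering acute adverse events of the four drug regimens".
- **What staff look for.** The same section continues: "The medical assistant will be provided with a complete list of possible adverse events of the respective drug". No common checklist for acute events is described.
- **Solicited events.** Field procedures plans a pre-tested questionnaire 48 h after treatment and describes its events as attributable to treatment. No drug-specific version is mentioned. The form in Appendix 4 is a figure that is not reproduced in the text available for review.
- **Masking.** Laboratory procedures blinds the technicians who read the slides and the FLOTAC apparatus. No section says whether the clinician, the medical assistant, the person giving the drugs, the interviewer or the children know the regimen. Both single-drug arms get a dummy for ivermectin; for example, "children will receive a single dose of mebendazole (500 mg) and a placebo resembling ivermectin". No dummy or matched tablet is described for albendazole against mebendazole. Appendix 3 has the drugs handed out from the randomized list and mentions no coded packs.
- **Analysis.** Data analysis: "the frequency and severity of acute and solicited adverse events of the different drug regimens will be compared".

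**The concern.** A comparison of adverse events between arms is fair only if every child is observed in the same way. A list that varies with the drug can do two things: prompt staff to look for different symptoms in different arms, and tell the person holding it what the child received. A requirement that an event be attributable to treatment, if applied when it is recorded, adds a judgement that may also vary by arm. The severity grades are partly observer-dependent too, because they refer to medication requested and intervention given.

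Most of the events that the plan expects are subjective: "Side effects can include fatigue, headache, dizziness, allergic reactions, shivering, abdominal pain, nausea, vomiting, diarrhea or fever". Safety is part of Objective 1, and the absence of safety data on mebendazole plus ivermectin is one of the stated reasons for the trial (Safety of the benzimidazoles; Significance). The background section itself records how earlier data were gathered: "Although not actively assessed, no adverse events were reported after mebendazole treatment". Randomisation does not correct unequal detection. A larger sample does not either; it only makes a given distortion more likely to reach significance.

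**Working it through.** **No plan figure to reproduce.** The plan gives no adverse-event rate and no sample size for safety. Its one sizing result, 105 per group, concerns the *T. trichiura* cure rate. It reproduces (the stated formula at 45% vs 65% gives 105.2) and has no bearing here.

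**The passages side by side**

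| Contrast | What could disguise it | What could reveal it |
|---|---|---|
| Single drug vs same drug plus ivermectin | Placebo resembling ivermectin, number of tablets by weight | A list matched to the regimen; sight of the randomized list |
| Albendazole vs mebendazole | Nothing described | The tablets, if they differ; the list; the randomized list |

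The text neither says that the observer knows the regimen nor prevents it.

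**Illustration 1: unequal detection.** The number per arm is 114, from the Appendix 8 flowchart (135 − 7 − 14 = 114). The rest is assumed: a true event rate p equal in both arms, full detection in one arm and a fraction s in the other. The observed rates are then p1 = p and p2 = s·p, and the apparent risk ratio is 1/s. For a two-sided 5% pooled test, with d = p1 − p2 and m = (p1 + p2)/2:

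- s0 = √(2m(1 − m)/n)
- s1 = √((p1(1 − p1) + p2(1 − p2))/n)
- P(significant) = Φ((d − 1.96·s0)/s1) + Φ((−d − 1.96·s0)/s1)

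Example with p = 20%, s = 0.7: p1 = 0.20, p2 = 0.14, d = 0.06, m = 0.17, s0 = √(0.2822/114) = 0.0498, s1 = √(0.2804/114) = 0.0496. This gives Φ(−0.76) + Φ(−3.18) = 0.225.

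| True rate | s = 0.9 (RR 1.11) | s = 0.8 (RR 1.25) | s = 0.7 (RR 1.43) | s = 0.5 (RR 2.00) |
|---|---|---|---|---|
| 10% | 6% | 8% | 13% | 30% |
| 20% | 7% | 12% | 23% | 56% |
| 30% | 8% | 18% | 34% | 78% |

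At 135 per arm the 20%, s = 0.7 entry rises from 23% to 26%.

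**Illustration 2: lists of different length.** Assume no drug effect and independent symptoms, each present by chance in a fraction b of children. A list of L items then finds at least one event in 1 − (1 − b)^L of them. Only the ten items come from the plan (the benefits and risks section); the shorter lengths and b are assumed. False-positive rates at 114 per arm, by exact enumeration of the pooled test:

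| Items | b = 1% | b = 5% |
|---|---|---|
| 9 vs 10 | 8.6% vs 9.6%: 6% | 37.0% vs 40.1%: 8% |
| 6 vs 10 | 5.9% vs 9.6%: 19% | 26.5% vs 40.1%: 59% |

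Slightly unequal looking barely matters; strongly unequal looking could create a difference on its own. The documents do not show which applies.

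**The case against.** A reader might infer that the planned comparison does measure what an unmasked observer knows, and that it will show a spurious excess in the combination arms because their lists are longest. The documents do not support that reading.

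- **The list holder.** The list goes to the medical assistant, while a clinician registers the events. That they are one person is plausible but not stated.
- **The purpose of the list.** The sentence that follows concerns medical action, so the list may be a clinical reference, or a set of lists for all study drugs held together.
- **Knowledge of the regimen.** No section says that the observer knows it. The ivermectin placebo may disguise precisely the contrast in which an excess would be predicted.
- **The placebo's origin.** The Conflict of interest section says that "the placebo (aspartam) were bought from pharmacies in Switzerland and France". Its content and source do not contradict its resemblance to ivermectin.
- **List length.** The only list in the documents is a common one for anthelminthic drugs. Nothing says that the combination arms have more items.
- **The 48 h questionnaire.** It may well ask every child the same questions. The form cannot be seen here, and that is not a fault of the plan.
- **The percentages.** They rest on assumed inputs, and an outcome of any acute event is not named in Data analysis.

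All of this stands, and it limits the conclusion to a bias that is not excluded. It does not remove the point. The plan as written does not require the same symptoms to be asked of every child in the hour after treatment, and the placebo does nothing for albendazole against mebendazole or against a list or allocation sheet that reveals the regimen.

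**Conclusion.** The point holds in limited form. With a list worded by drug, registration by the clinician who supervises intake, and blinding stated only in the laboratory, the plan leaves room for unequal ascertainment of subjective acute events between regimens. The argument from the list concerns acute events. For solicited events, what remains is the attribution wording and the silence on whether the interviewer is masked.

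The size cannot be derived from the documents. Under the assumed detection ratios the false-positive rate runs from 6%, close to nominal, to 78%. These figures show how sensitive the comparison is; they do not estimate what will happen. The efficacy outcomes, read by blinded technicians, are not affected. This is a cheap improvement to make, not a reason to discard the safety comparison.

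**What to change.** In Field procedures:

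1. Replace the list worded by drug with one identical checklist for all four regimens: the ten symptoms named in the benefits and risks section, plus free text.
2. Mark each item present or absent for every child at both assessments, whether or not it is thought to be caused by treatment. The comparison of randomised arms then shows what is drug-related.
3. Use a recording form that carries only the child's ID. Keep the randomized list with the health worker who gives the drugs and off the recording form, with the regimen available whenever care requires it.
4. State who, besides the laboratory, is masked, and to which contrast.

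The clinician's supervision on site stays as it is. Relocating the clinician is not part of this fix: item 6 of the study-area selection criteria uses the same empty classrooms for treatment and observation.

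The timing of the two assessments must also be reconciled before the form is finalised. Field procedures gives 1 h and 48 h, Data analysis gives 3 h and 72 h, and Appendix 3 gives 3 hours and 3 days.

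The cost is one common form and a rule on who holds the list, with no extra visits or children. The small downside is that more unrelated symptoms are recorded.
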